### 1560 1561 4.3 Complier average causal effects (CACE) population

1562 A secondary analysis will be undertaken, using a CACE analysis to determine the effect of receiving the  
1563 intervention, rather than merely being randomised to receive it. For the purposes of this analysis, we define  
1564 “receiving the intervention” to mean that the family has attended at least four of the six planned intervention  
1565 visits, and “not receiving the intervention” as receiving zero to three sessions. These first four sessions relate to  
1566 delivery of the core intervention, with the extra two sessions being booster sessions. Delays to the planned  
1567 schedule will not be considered a protocol violation, so long as at least four of the six planned intervention visits  
1568 were completed before the outcome is assessed. Initially all families in the control group will be analysed as not  
1569 receiving the intervention (unless, off protocol, they receive at least four sessions of the ViPP intervention).

1570 A sensitivity analysis will be undertaken on this CACE analysis, where families who receive some other video  
1571 feedback intervention during the study (off protocol) will be analysed as if they received the intervention (unless  
1572 we know that they received an incomplete course, and that this incomplete course consisted of no more than  
1573 three sessions).

1574 A further CACE analysis will be performed, to determine the effect of receiving the intervention to a high level  
1575 of fidelity, rather than merely being randomised to receive it (and rather than receiving it with poor fidelity). To  
1576 count as receiving the intervention, families would have to receive at least four sessions with a mean level of  
1577 fidelity above the 25th centile (and then above the 50th centile) of the distribution of fidelity scores within this  
1578 randomized trial.

1579

1580 **Change from official signed draft:** previously there was a per protocol population definition described here,  
1581 rather than a complier average causal effects population.

1582 **Change from version 1 to version 2:** a new CACE analysis is added which refers to fidelity as well as to  
1583 number of sessions received.

1584

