### 1502 3.6 Sample Size

1503 The total sample size will be 300 participants.

1504 If losses to follow-up are 20%, this leaves 120 participants per group with follow-up data. We would then have  
1505 80% and 90% power to detect standardised effect sizes of 0.36 and 0.42 respectively, at the 5% significance  
1506 level, using an independent samples t-test. In addition, we have stated that our analysis will adjust for baseline  
1507 behavioural score, research centre and age of child, and parental involvement (one versus two) which will  
1508 increase power, probably to over 90% for the 0.36 effect size (since such adjustment will reduce the residual  
1509 error variance in our model). Kahan and colleagues (2014, ref 1) found that covariate adjustment for 1 to 4  
1510 variables in trials increased power from 80% to a median of 93% power in their sample of 12 outcomes assessed  
1511 across 8 studies.)

1512 We have conservatively allowed for a potential drop-out rate of 20% because of the longer follow-up time in the  
1513 proposed study, even though previous intervention studies detailed below have maintained retention rates of  
1514 over 90% at follow-up.

1515 The pooled effect size for all randomised controlled trials to date that have used the same video feedback  
1516 intervention (ViPP) is 0.46 ([name], 2013, personal correspondence). Other relevant literature  
1517 for interventions for behavioural problems, predominantly in slightly older children, yield higher effect size  
1518 estimates. In the systematic reviews undertaken for the most recent NICE guidance on conduct disorders in  
1519 children and young people (ref 2), the pooled effects for parent-focussed interventions yielded estimated effect  
1520 sizes of 0.69 standard deviations for researcher-rated outcome (the main outcome measure in the proposed  
1521 study), and 0.54 for parent-rated outcome. In a study of the Incredible Years programme in 2-9 year olds (ref 3)  
1522 effect sizes ranged from 0.48-0.78. In the SPOKES trial (ref 4) of intervention for parents of 6 year olds, the  
1523 effect size for behavioural outcomes was 0.52 SD difference between the treatment and control group. Where  
1524 parenting programmes have been rolled out across the UK (ref 5-6) similar effect sizes have been found, albeit  
1525 in non-randomised designs (effect sizes ranged from 0.44-0.71).

1526

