### 6.3 Complier average causal effects analysis

This will be performed by two stage least squares regression analysis on **PPACS**. The definitions for compliers and non-compliers/treatment not received is given in 4.3. As is standard practice for CACE analysis, it is assumed that there is no effect of being randomized to a particular group, other than the effect that results from receiving the intervention in practice (with at least 4 visits).

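### The fidelity-threshold CACE analyses code lower-fidelity completers as untreated, so the estimate grows with the cut-off whether or not fidelity matters (overstatement of up to about 1.33-fold and 2-fold)

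*Combined protocol and SAP*

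**What the plan says.** SAP 4.3 first defines receipt as attending at least four of the six visits; zero to three sessions is non-receipt. On the control arm it says "Initially all families in the control group will be analysed as not" having received it, with an exception for four or more ViPP sessions obtained off protocol.

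Version 2.0 then adds an analysis aimed at delivery with high fidelity. Its contrast is with allocation alone and also with delivery at low fidelity. To "count as receiving the intervention, families would have to receive at least four sessions with a mean level of" fidelity that exceeds a cut-off. The cut-off, applied at two levels in turn, requires "fidelity above the 25 th centile (and then above the 50 th centile) of the distribution of fidelity scores within this" trial.

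SAP 6.3 gives the estimator: "This will be performed by two stage least squares regression analysis on" PPACS, with receipt as defined in 4.3. It states the exclusion restriction once: "it is assumed that there is no effect of being randomized to a particular group". The one path that it allows is set out as an exception: "other than the effect that results from receiving the intervention in practice (with at least 4 visits"). That statement contains no fidelity term and is not restated for the fidelity versions.

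Neither document defines the fidelity score. SAP Table 8.15 (therapist report) and Table 8.16 (independent assessment, visits 1 to 4) list elements completed. Protocol 7.1.1 has independent raters assess only a random proportion of sessions. The footnote to the CACE results table (Table 8.8) describes a regression on randomised group, which is the ITT model.

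**The concern.** A family that attended four, five or six sessions but scored below the cut-off is coded in the same way as a family that attended none. 2SLS then takes allocation to have had no effect on that family. By the wording of 6.3, such a family lies on the path through which the intervention works.

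What is at stake is interpretation. The report could show three CACE estimates that rise in steps: at least four sessions, above the 25th centile, above the 50th centile. That looks like a dose-response to fidelity. The steps are set by how many families each definition codes as treated, and the relation between fidelity and outcome plays no part in them.

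**Working it through.** **The plan's own figures.** SAP 3.6 states: "If losses to follow-up are 20%, this leaves 120 participants per group with follow-up data. We would then have" 80% and 90% power for effects of 0.36 and 0.42 SD. A two-sided 5% comparison of means with 120 per arm gives 79.6% and 90.2%, and 240/(1 − 0.2) = 300. These reproduce. The documents give no figure for the CACE analyses.

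**Inputs.**
- ITT effect 0.36 SD, taken from SAP 3.6 for illustration.
- p = share of the intervention arm with at least four sessions. Not given; assumed 0.7, 0.8 and 0.9.
- q = share of those families above the cut-off: 0.75 and 0.50, if the centiles are of family mean scores among families with at least four sessions (assumption).
- Control receipt: zero.
- r = effect in lower-fidelity receivers divided by effect in higher-fidelity receivers. Unknown; varied from 0 to 1.

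**Step 1: what 2SLS returns.** With one binary instrument, the estimate is ITT / [P(coded treated | ViPP) − P(coded treated | control)]. The four-session CACE is ITT/p and the fidelity CACE is ITT/(pq). Their ratio is 1/q, that is 1/0.75 = 1.33 and 1/0.50 = 2.00. Both p and the outcome data cancel. With p = 0.8:
- at least four sessions: 0.36/0.80 = 0.45
- above the 25th centile: 0.36/0.60 = 0.60
- above the 50th centile: 0.36/0.40 = 0.90

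**Step 2: the estimates do not depend on what fidelity does.** Suppose 85% attend at least four sessions and the average effect among them is −0.36 SD, so ITT = 0.85 × −0.36 = −0.306. The three estimates are −0.306/0.85 = −0.36, −0.306/0.6375 = −0.48 and −0.306/0.425 = −0.72. Simulation (2,000 trials per scenario, 150 per arm) gave these values to within 0.01 in each of three cases: fidelity irrelevant, all benefit above the median, and all benefit below the median.

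**Step 3: overstatement of the true high-fidelity effect.** If τ is the effect in high-fidelity receivers, ITT = pτ[q + (1 − q)r]. Dividing by pq gives τ[1 + ((1 − q)/q)r].

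| r | 25th centile | 50th centile |
|---|---|---|
| 0 | 1.00 | 1.00 |
| 0.25 | 1.08 | 1.25 |
| 0.50 | 1.17 | 1.50 |
| 0.75 | 1.25 | 1.75 |
| 1 | 1.33 | 2.00 |

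**Step 4: test statistic.** In 3,000 simulated trials (120 per arm, fidelity irrelevant, baseline covariate correlated 0.6 with outcome), mean estimates at p = 0.8 were −0.451, −0.605 and −0.907, with mean t of −3.50, −3.40 and −3.25. The ratios were 1.34 and 2.01 at p = 0.7, 0.8 and 0.9. The level of t depends on the assumed covariate adjustment. Unadjusted, with 150 per arm and 85% receipt, it is about 0.306/√(2/150) = 2.65. Its near-constancy across definitions remains: −2.64, −2.61 and −2.55 in simulation.

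**Step 5: the centile reading.** If the reference set is single-session scores (assumed normal, six sessions, within-family correlation 0.2 to 0.8), the share of families above the 25th centile is Φ(0.674/√(ICC + (1 − ICC)/6)) = 88% to 77%. The upper end is then 1.14 to 1.30. The 50th-centile figure stays near 2.

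**The case against.** The strongest reply has four parts.

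1. This is a further analysis within a secondary analysis. No hypothesis, sample size or decision in the plan rests on it, and Table 8.8 gives it no rows of its own. This stands and limits the severity. A reader might infer that the trial's main conclusion is compromised. The documents do not support that, because the primary analysis is ITT.

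2. The exclusion restriction is not broken as a matter of logic. It holds if four or more lower-fidelity sessions do exactly nothing. This also stands. A reader might infer that the estimates are certain to be inflated 1.33-fold and 2-fold; those are the values at r = 1, and the documents do not give r. But the SAP neither states nor justifies a zero effect, and 6.3 points the other way.

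3. The 1.33 depends on a reading of the centile that the SAP does not settle. Agreed; Step 5 shows the alternative. The undefined score also cuts the other way: ties at the top of the scale, or coding unrated families as untreated, would shrink the denominator further.

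4. Confidence intervals widen along with the estimates, so a careful reader would not be misled. This is only partly right. Interval and estimate stretch together, the test statistic hardly moves, and the rising point estimates remain.

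The four-session CACE has the same weakness, to a smaller degree, for families with one to three sessions.

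**Conclusion.** The fidelity-threshold analyses are wrong as written and should be fixed; this is not a threat to the trial's main result. They divide one ITT effect by a smaller share of families and so cannot show whether fidelity matters. The growth of the estimate relative to the four-session CACE is mechanical, in inverse proportion to the share above the cut-off, and applies in absolute size whichever way the ITT effect points.

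The bias against the true high-fidelity effect is the range in Step 3. It rests on r between 0 and 1, no control receipt, and centiles of family means among families with at least four sessions. Attendance does not affect it. If lower-fidelity delivery worked better than higher-fidelity delivery, the overstatement would exceed the upper ends; nothing in the documents suggests or excludes that.

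**What to change.** In SAP 4.3 and 6.3:

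- Remove the two fidelity-threshold 2SLS analyses as estimates of the effect of high-fidelity receipt. If they are kept, state that they assume zero effect of four or more lower-fidelity sessions; define the fidelity score, its source, its reference set and the handling of unrated families; and report ITT/(p[q + (1 − q)r]) over a range of r. With ITT 0.36 and p = 0.8, r = 0, 0.5 and 1 give 0.60, 0.51 and 0.45 for the 25th centile, and 0.90, 0.60 and 0.45 for the 50th.
- Keep the four-session CACE, noting that it assumes no effect of one to three sessions. Add a 2SLS with receipt defined as at least one session, for which the restriction is more credible. A version using sessions attended (0 to 6) is optional and must state its linear dose-effect assumption.
- Report any association between fidelity and outcome within the ViPP arm as observational, adjusted for baseline PPACS and centre.
- Rewrite the Table 8.8 footnote to describe the 2SLS model.

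The cost is SAP wording and no new data. A fidelity-specific causal estimate is lost or becomes a range.

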## 1585 5 Variables of Analysis

### 1586 5.1 Primary Efficacy Variable

1587 The severity of behavioural problems will be assessed using the PPACS interview to the primary care-  
1588 giver and standard PPACS scoring method. This will be collected at 5 months (primary outcome is at  
1589 this time point) and at 24 months after randomisation.

1590

### 1591 5.2 Secondary Efficacy Variables

1592 These will be collected at 5 months and at 24 months after randomization.

- 1593 1) Child Behaviour assessed by the CBCL questionnaire (total score), as assessed by primary and, if  
1594 possible, secondary care-givers.
- 1595 2) Strengths and Difficulties Questionnaire (SDQ) relating to qualities of the child, to be completed  
1596 by primary and, if possible, secondary care-givers.
- 1597 3) Strengths and Difficulties Questionnaire (SDQ) relating to qualities of the child, as assessed by a  
1598 nursery teacher/ care-giver from outside the family (only at 2 years follow-up).
- 1599 4) Parental couple functioning assessed by the Revised Dyadic Adjustment Scale (RDAS), for each  
1600 parent/ care-giver when two are engaged in the study.
- 1601 5) Parental mood assessed by the Patient Health Questionnaire 9 (PHQ9), for each parent/ care-giver  
1602 when both are engaged in the study.
- 1603 6) Parenting practice assessed by the Parenting Scale, for each parent/ care-giver when both are  
1604 engaged in the study.
- 1605 7) Health and social care services provided to the child and services parents/care-givers have  
1606 attended in relation to their child's needs, using a modified version of the Child and Adolescent  
1607 Service Use Schedule (CA-SUS).
- 1608 8) Parental anxiety assessed by the Generalized Anxiety Disorder 7 (GAD7) for each parent/ care-  
1609 giver when both are engaged in the study.
- 1610 9) Parental sensitivity and engagement will be assessed, if we are able to secure an additional grant  
1611 beyond the HTA grant to fund the collection of this data (based on detailed assessment of  
1612 interviews).

1613

### 1614 5.3 Safety Variables

1615 There are no obvious adverse events that are expected to be related to the ViPP intervention and the risk to  
1616 participants is believed to be low. We have therefore not specified any particular type of adverse events in  
1617 advance, other than serious adverse events, for routine collection. Information on all serious adverse events  
1618 affecting any family members who are participating in the study (i.e. the child and the one or two participating  
1619 care-givers) will be collected for the duration of the follow-up period, irrespective of the likely connection to the  
1620 intervention. Information on mild to moderate adverse events will be collected only if the event might plausibly  
1621 be attributable to the intervention.

1622 It is important to note that some adverse events (such as incarceration or death of sibling) may be reported  
1623 indirectly, through the process of re-scheduling appointments, for example, rather than directly as an adverse  
1624 event. The database notes columns will be scrutinised prior to analysis in order to identify these. Hospitalisation  
1625 of the child, will be collected via the CASUS form which is designed to collect health care utilisation data for  
1626 the economic analysis.

1627

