### 12.4.2. Reporting of SAEs

Due to the low risk nature of this study, AEs that do not meet the above Seriousness criteria will not be collected during the study.

Rapid reporting of all SAEs occurring during the study must be performed as detailed in SAE reporting instructions. SAEs will be reported via the eCRF within 24 hours of becoming aware of the event. All reported SAEs will be reviewed by the Chief Investigator (or designee) within 2 working days of receiving notification of the SAE report. The SAE review will be recorded on the eCRF.

SAEs will be followed up until they are resolved.

If the investigator becomes aware of safety information that appears to be related to the treatment, involving a participant who participated in the study, even after an individual participant has completed the study, this should be reported to the Sponsor.

725 12.5 Definition of a Serious Adverse Reaction (SAR)

726 A SAR is defined as a SAE that is judged to be related to the trial treatment.

727 **12.6 Definition of Unexpected and Related Serious Adverse Events**

728 A Related and Unexpected Serious Adverse Events is an Adverse Event that is classed as serious, is suspected to

729 be caused by the trial treatment and is unexpected i.e. not listed as an 'expected SAE' in this protocol.

730 **12.6.1 Reporting of Related and Unexpected Serious Adverse Events**

731 All Related and Unexpected Serious Adverse Events will be notified to the Research Ethics Committee (REC)

732 and the Sponsor within 15 days of becoming aware of the event.

733 Follow up of participants who have experienced a Related and Unexpected Serious Adverse Event should

734 continue until recovery is complete or the condition has stabilised.

735 **12.7 Annual reporting of SAEs**

736 Annual safety reporting will be included in the annual progress report sent to the REC, on the anniversary of

737 Ethics approval each year.

738

739 **13. STATISTICAL ANALYSES**

740 **13.1. Sample Size and power considerations**

741 The total sample size will be 300 participants.

742 If losses to follow-up are 20%, this leaves 120 participants per group with follow-up data. We would then have

743 80% and 90% power to detect standardised effect sizes of 0.36 and 0.42 respectively, at the 5% significance

744 level. In addition, we have stated that our analysis will adjust for baseline behavioural score, research centre and

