### 1554 1555 4.2 Safety population

1556 The safety population will be children and their parents/ care-givers who have received at least one intervention  
1557 as part of the ViPP programme, compared to those allocated to the control group who have not received any  
1558 ViPP intervention. Adverse events will be compared between arms according to these safety definitions of  
1559 groups.

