## 1792 6.5 Safety Analysis

1793 A table of serious adverse events and any adverse events considered to be relevant will be produced, by type of  
1794 event and by treatment received.

1795 The table will show numbers of children who have at least one such adverse event of a given type and then  
1796 numbers of families where at least one parent/care-giver is affected by this type of adverse event. Percentages  
1797 (of children/ families) will be calculated and presented. Proportions will be compared between treatment groups  
1798 using Fisher's exact test.

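### Mild to moderate adverse events are recorded under an attribution filter yet tested between groups, the protocol says they are not collected at all, and the only planned SAE comparison omits ViPP families who never start

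*Combined protocol and SAP*

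**What the plan says.** **Collection of non-serious events.** SAP 5.3 (Safety Variables) states: "Information on mild to moderate adverse events will be collected only if the event might plausibly" "be attributable to the intervention". Protocol 12.4.2 (Reporting of SAEs) states: "Due to the low risk nature of this study, AEs that do not meet the above Seriousness criteria will not be collected" during the study.

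**Collection of SAEs.** Under SAP 5.3, all SAEs in the child and the participating care-givers are collected throughout follow-up, whether or not they seem connected to the intervention. Protocol 12.4.2 requires them to be entered in the eCRF within 24 hours of awareness. Both assessment schedules list SAEs at every visit, and SAP 5.3 takes hospitalisation of the child from the CA-SUS.

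**Events found in notes.** SAP 5.3 adds that some adverse events may be reported "indirectly, through the process of re-scheduling appointments, for example, rather than directly as an adverse" event, and that the notes columns of the database will be searched for these before analysis.

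**Population and test.** SAP 4.2 sets "children and their parents/ care-givers who have received at least one intervention" session of ViPP against families allocated to control who received none. SAP 6.5 places SAEs and other relevant adverse events in one table by treatment received: "Proportions will be compared between treatment groups" with Fisher's exact test. Table 8.17 uses the same column definitions, and its single p-value column serves both kinds of row. No safety table by allocated arm is planned.

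**The concern.** There are three separate problems.

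1. Fisher's test compares recorded proportions. It says something about harm only if an event of a given kind is equally likely to be recorded in either group. A filter on plausible attribution to ViPP works against that, because a family that was never offered ViPP gives little reason to attribute anything to it. The likely distortion is against ViPP.
2. The protocol and the SAP disagree on whether these events are collected at all, so a reader cannot tell whether an empty row means no events or no collection.
3. The SAE rows escape the attribution filter but depend on the treatment-received grouping. A ViPP-allocated family that never starts disappears from the table. An SAE soon after randomisation that prevents a family from starting is therefore lost in ViPP, while the same event in a control family counts. If never-starters are at higher risk, this flatters ViPP.

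The first and third problems push in opposite directions. The safety conclusion is at stake; the primary efficacy result is not affected.

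**Working it through.** The documents give no safety rate to reproduce. The inputs taken from them are 150 families per arm (protocol, Trial Summary), a 5% significance level (SAP 6.1; two-sided assumed) and the timing of session 1 (protocol 11.7). Every event rate, capture probability and never-starter share below is an assumption. Rejection rates come from exact binomial enumeration of the two-sided Fisher test.

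**Step 1: unequal capture of non-serious events, no true difference, 150 v 150.** The recorded rate is the true rate multiplied by the capture probability. Chance of p ≤ 0.05:

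| True rate | Capture ViPP / control: 50% / 50% | 50% / 25% | 50% / 10% | 50% / 0% |
|---|---|---|---|---|
| 5% | 1.6% | 3.8% | 9.6% | 17.5% |
| 10% | 2.4% | 11.9% | 39.6% | 76.6% |
| 20% | 3.3% | 29.8% | 80.2% | 99.8% |

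With equal capture the test keeps its level. With unequal capture the error grows with the true rate and with the capture gap; at a true rate of 5% and a twofold gap it stays under 5%. The counts needed are small: a split of 5 v 0 gives p = 0.060 and 6 v 0 gives p = 0.030.

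**Step 2: window for losing an early SAE.** Session 1 is scheduled at day 14-28, plus or minus 7 days. The window therefore runs from 14 − 7 = day 7 to 28 + 7 = day 35 after randomisation. Until that session takes place, a ViPP-allocated family is in neither safety group.

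**Step 3: effect of removing never-starters on the SAE rows.** Let r be the true risk in each randomised arm, f the share of ViPP families who never start, and k their risk relative to starters. The risk shown for ViPP is r / (1 − f + f·k), so the risk ratio shown is 1 / (1 − f + f·k):

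- f = 10%, k = 2: 1 / (0.90 + 0.20) = 0.909
- f = 10%, k = 3: 1 / (0.90 + 0.30) = 0.833
- f = 15%, k = 2: 1 / (0.85 + 0.30) = 0.870
- f = 15%, k = 3: 1 / (0.85 + 0.45) = 0.769
- k = 1, any f: 1.000, no bias

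In absolute terms, with 135 or 128 ViPP families against 150 controls:

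| SAE risk r | Shift in ViPP risk (percentage points) | Fisher rejection rate |
|---|---|---|
| 5% | 0.45 to 1.15 | 3.8% to 5.5% |
| 10% | 0.91 to 2.31 | 4.6% to 7.9% |

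**Step 4: protocol against SAP.** The two collection rules cannot both hold. If protocol 12.4.2 governs, the non-serious rows of Table 8.17 should be empty and Step 1 has no object. If SAP 5.3 governs, Step 1 applies.

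**The case against.** The strongest defence is that the SAP does not present this table as a randomised comparison. SAP 6.5 states that it is by treatment received, Table 8.17 labels its columns accordingly, and such a safety set is common practice. The exclusions also fall on both sides, since control families who received any ViPP leave the control column. This stands as far as it goes. But SAP 4.2 still describes the comparison as one between arms, it carries p-values, and nothing by allocated arm sits beside it.

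Three stronger readings are tempting, and the documents do not support them.

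- **That the control rate is zero by definition.** A reader might infer this from the attribution rule. The wording is that an event might plausibly be attributable, which can be read as a filter on the kind of event and applied in either arm. Outcome assessors are blinded (protocol 11.3 and 11.5), so they should not be applying an arm-specific rule at visits. Lower capture in control is likely; zero capture is inference.
- **That re-scheduling notes inflate SAEs in ViPP.** SAP 5.3 speaks of some adverse events, and its examples are incarceration and the death of a sibling. The first is not a listed seriousness criterion in protocol 12.4.1, and a sibling is not among the participants whose SAEs are collected. The SAP does not say which appointments are meant, and assessment visits are arranged in both arms. ViPP families may have more appointments that generate notes, and no more than that can be said.
- **That the SAE comparison is known to favour ViPP.** This requires never-starters to be at higher risk. The documents give neither their number nor their risk.

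It is also fair to say that both documents regard the trial as low risk and that no stated decision turns on this p-value.

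**Conclusion.** The concern holds in a limited form. The conflict between protocol 12.4.2 and SAP 5.3 is a matter of record and needs no assumption. If the SAP rule is followed, the Fisher p-value for non-serious events does not reflect a like-for-like comparison. How far it misleads depends on capture rates that the documents do not give: under the assumed figures the false-positive rate runs from below 5% to nearly 100%.

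For SAEs the attribution filter plays no part. The weakness is the treatment-received grouping with no comparison by allocated arm. Its effect is of unknown size and nil if never-starters have average risk. It is modest under the assumed inputs: a risk ratio of 0.91 to 0.77, or at most about 2.3 percentage points at a 10% SAE risk. The change is worth making because it is cheap and removes a doubt that the reported table could not settle.

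**What to change.** 1. Reconcile protocol 12.4.2 and SAP 5.3 so that both state which non-serious adverse events, if any, are collected.
2. Report any non-serious events collected under the attribution filter descriptively, and remove the Fisher test from those rows of Table 8.17.
3. Add an SAE comparison of all randomised families by allocated arm. Use every SAE source: eCRF rapid reports, SAE items at assessment visits, and child hospitalisation from the CA-SUS. Restricting it to visit items and the CA-SUS would lose SAEs reported through the eCRF, particularly in families who miss visits. Keep the treatment-received table as supplementary.
4. Flag events found only through database or re-scheduling notes, so that any difference in the opportunity for detection is visible.

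The cost is a clarifying sentence in the protocol, SAP wording and one extra table. No new data are needed, because SAEs are already collected in both arms throughout follow-up.
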